## 6.6 Ethical considerations

No specific personal insurance nor travel accident insurance will be effected. The study protocol will be reviewed by the competent ethics committee.

## 6.7 Information of the subjects

The information leaflet for the subjects, the questionnaire, and the consent form are annexed.

# Methods for the assessment of effectivity and safety

## 7.1 Risks and side effects

The risks correspond to the common risks of a radius fracture operation.

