# 2 Introduction

## 2.1 Summary

The distal radius fracture is one of the most common disease patterns in trauma surgery with an incidence of two to three per 1,000 inhabitants. It is a distal fracture of the radius. As it is located close to the wrist, it is commonly referred to as a broken wrist. It occurs in all age groups, but mostly between 6 and 18 years and between 60 and 70 years. The formation mechanism is triggered by a traumatic fall on the extended (Colles fracture), or, more rarely, on the bent wrist (Smith fracture). In children, the distal radius fracture occurs mainly during sports. In adults, however, it is mainly caused by tripping and falling the on uneven or slippery ground. The goal of every therapy, either conservative or operative, is the anatomical reconstruction of the joint surface. Unstable extraarticular and intraarticular fractures are mostly stabilized by plate osteosyntheses, which are mostly fixed to the flexor side, rarely also to the extensor side of the radius close to the wrist. The main advantage of plating is the immediate practice safety, so that the physiotherapy can be started shortly after the postoperative application of the cast,. An early mobilisation can prevent the negative consequences of joint immobilization, like e.g. muscular atrophies, joint immobilisation, tendon conglutination, and capsule contraction. Several studies have demonstrated that the immobilisation provokes a considerable degree of muscular atrophy, especially during the first two weeks. Moreover, it causes metabolic, neurological, and functional adaptations, so that the muscular strength may decrease by half after 4-6 weeks of immobilisation in the cast. A possible solution for this problem is the use of a dynamic vacuum orthesis: It provides the stability of a circular forearm splint, and which therefore allows for an early low-risk increase of load, as well as for a limited mobility in the wrist. Furthermore, the comfort of the patients is increased by the fact that an othesis is less heavy than a splint and can be easily applied by the patient himself after having received an instruction. This enables a regular body care. Besides, the limited mobility of the wrist allows for establishing a more physiological functional image. Moreover, a favourable progress of the postoperative phase could reduce the period of disability in the workforce.

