## 5.2 Inclusion criteria

- At least 18 years old
- AO2.3 A2, A3, B1, B2, B3, C1, C2 fractures requiring surgery, which have been treated with a volar angular stable plate (2.4mm, 3.5mm, alle types)
- Soft tissue G0, G1
- Patients have to be able to actively support the postoperative treatment.

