# Course of the study and methods of investigation

## 6.1 Clinical examinations

Clinical examinations will be carried out in order to confirm the diagnosis, as a control, and to evaluate the satisfaction of the patients as well as the evolution of pain.

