## 6.3 Planned testing

Regular clinical follow-up examinations and controls as well as targeted surveys regarding pain and patient satisfaction are planned. Based on these data, both methods can be compared to each other.

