## 6.4 Implementation and finalization

The participation at this study is entirely voluntary. A patient can revoke his consent to his participation in the study at any time without stating reasons. Preoperatively, appointments for reevaluation are fixed 1, 2, and 6 weeks postoperatively. Moreover, the patients should know that, after 1, 2, and 6 weeks, as well as after 6 months, he has to fill out a questionnaire and that a clinical control will take place. Only, if a patient agrees to these conditions, he can be included in the study. For those patients, which have agreed to participate in the study, closed envelopes are deposited in the operating theatre. Each envelope contains a piece of paper reading “VacoHand” or “splint”. Depending on the envelope, the patient has to wear initially the VacoHand® or the splint for 1 week in total (unless the operating surgeon indicates otherwise). Then, 1 week postoperative, the splinting is changed from the forearm splinting to the VacoHand® and vice versa.

[figure not shown]

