## 6.5 Data protection

The patient data are registered and stored in a database at the Clinic for Trauma and Restorative Surgery, BG Klinik Tübingen. The deletion of the data, which are related to the study, is scheduled to take place in 10 years. Only the principal investigator and the authors of this study as well as research associates which have been selected by the authors of the study are authorized to access these data. The data will only be shared only in a pseudonymized fashion, if necessary. In case of a drop out or of the revocation of the permission by the patient, the data will be completely deleted. For the publications resulting from this project, only pseudomynized data will be used.

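### The safety section describes only the risks of the operation, which both devices share, and no section plans to record complications as a safety outcome by device worn

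*Protocol*

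**What the plan says.** Protocol section 7.1 is the only subsection of the chapter on methods for assessing effectiveness and safety. Its full content is: "The risks correspond to the common risks of a radius fracture operation".

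The operation is a condition of entry. Section 5.2 admits "fractures requiring surgery, which have been treated with a volar angular stable plate". What is allocated is the aftercare. Under section 6.4, "the patient has to wear initially the VacoHand® or the splint for 1 week in total", and at one week "the splinting is changed from the forearm splinting to the VacoHand® and vice versa". The operating surgeon may direct otherwise.

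The introduction (2.1) says that the orthosis "allows for an early low-risk increase of load, as well as for a limited mobility in the wrist", and that patients can put it on themselves after instruction.

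On data collection, section 6.3 states: "Regular clinical follow-up examinations and controls as well as targeted surveys regarding pain and patient satisfaction are planned". Section 6.1 says that the examinations confirm the diagnosis, act as a control and serve "to evaluate the satisfaction of the patients as well as the evolution of pain". Section 3 and the synopsis name SF-36 as primary and DASH, Neutral-0 and length of disability as secondary. Visits are at 1, 2 and 6 weeks and 6 months.

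Section 6.5 adds: "In case of a drop out or of the revocation of the permission by the patient, the data will be completely deleted". The Data management chapter repeats this rule.

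**The concern.** Section 7.1 describes a risk that is common to both devices and gives no method for measuring any other. If the devices differ in complications, no planned outcome is designated to show it. One device could then be preferred on patient-reported outcomes with no tabulated evidence on harm beside that preference.

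Two features of the design make this harder to repair afterwards. After the swap, a complication cannot be assigned to a device unless its onset and the device then worn were written down. And a patient who leaves because of a complication is removed from the data altogether, so whatever harm information survives leans towards patients who tolerated the device.

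This is a matter of data collection. An analysis plan cannot recover events that were never recorded or have been deleted.

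**Working it through.** The plan gives no safety figure to reproduce, so the main check is textual.

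**Step 1. Can the risk named in 7.1 differ between devices?** Plating is required of every patient (5.2), and the device is assigned by envelope and then swapped (6.4). Operative risk is therefore common to both devices.

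**Step 2. Does another section plan to record harms?**

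| Item | Where | Records complications as a safety outcome? | Records device at onset? |
|---|---|---|---|
| SF-36 | Synopsis, 3 | No | No |
| DASH, Neutral-0, length of disability | Synopsis, 3 | No; may reflect consequences | No |
| Clinical examinations and controls | 6.1, 6.3, 6.4 | Not stated; may reveal some | No |
| Pain and satisfaction surveys | 3, 6.1, 6.3 | No; pain may reflect some | No |
| Safety chapter | 7.1 | No | No |

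**Step 3. Could a harm noticed at a visit be attributed without a record of onset?**

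- Week 1: largely yes. The visit coincides with the swap, so a harm seen then belongs to the first device, unless the surgeon had directed otherwise.
- Week 2: not reliably. The harm may have begun under either device, and 6.4 gives no duration for the second.
- Week 6 and month 6: no. The patient has been exposed to both, so a harm without an onset date can be compared only between sequences.

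**Step 4. What happens to those who leave?** Sections 6.5 and Data management delete the data on drop-out, so a drop-out caused by a complication leaves no trace in the results.

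**Step 5. How informative could proper recording be?** The input is 50 planned patients (synopsis). With zero events in n patients, the exact upper limit solves (1 − p)^n = a, so p = 1 − a^(1/n).

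- One-sided 95% (a = 0.05): 1 − 0.05^(1/50) = 0.058, or 5.8%.
- Two-sided 95% (a = 0.025): 1 − 0.025^(1/50) = 0.071, or 7.1%.
- The shortcut 3/50 = 6% approximates the one-sided limit.

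This is a best case. It needs all 50 patients to be evaluable on the device and events to be recorded by device. The exposure is about one week for the first device and unstated for the second, and harm carried over from the first period is ignored.

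For late harms, compared by sequence, an equal split (an assumption; no ratio is stated) gives 50/2 = 25 patients per sequence. The limits are then 1 − 0.05^(1/25) = 11.3% and 1 − 0.025^(1/25) = 13.7%.

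**The case against.** The strongest reply is that the trial does look at its patients. There are four clinical controls, pain surveys, a function score, range of motion and length of disability, and the week-1 control falls at the swap. A reader might infer from 7.1 that device harms would go wholly unseen. The documents do not support that: some harms would show indirectly. What remains is that none is planned to be recorded as an event or tied to a device.

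Second, a reader might infer that the protocol itself identifies extra harms from the orthosis. It does not. The introduction presents load, wrist movement and self-application as advantages and credits the orthosis with the stability of a circular splint. Skin damage, nerve symptoms and loss of reduction are not named as device risks anywhere. That such harms could arise is an inference from those features and must be labelled as one.

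Third, the stated aim is satisfaction, with function and disability as secondary endpoints. Testing the introduction's remark about low risk is not an objective, so leaving it untested contradicts no stated goal. This stands. It does not explain why a chapter on assessing safety contains no assessment.

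Fourth, the deletion rule is a fault in its own right. It matters here only because it would also remove harms that led to drop-out; it should not be used to raise the weight of this point.

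The annexed patient information form is not shown. It may list device risks, but telling patients about risks is not a method of recording them.

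**Conclusion.** The point holds in this form: section 7.1 equates the trial's risks with those of an operation common to both devices, and no section plans to record complications as a safety outcome or to attribute them to the device worn. Followed as written, the protocol yields no device-attributed harm data and loses patients who drop out because of a complication.

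The primary endpoint can still be analysed, so this is something that should be changed rather than a fatal defect. The size of any harm missed cannot be estimated, because the documents give no event rates. The limits of 5.8% and 7.1% describe what a corrected trial could exclude at best. They do not measure the damage done by the gap.

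The conclusion rests on the visible text, without the annexed forms, and on the assumption that the devices may carry harms of their own. It does not say that either device is unsafe.

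**What to change.** 1. Replace section 7.1 with a recording rule. At each of the four planned visits (1, 2 and 6 weeks, 6 months), record device-related events with onset date and the device worn at onset. Examples are skin or pressure damage, swelling or nerve symptoms, loss of reduction on any image taken in routine care, re-operation, and unplanned removal or change of device. Report events by device worn at onset while a device is worn, and by sequence afterwards, for all allocated patients.
2. Amend section 6.5 and the Data management chapter together, so that data collected before a drop-out are kept and analysed. Treat revocation of consent separately, under the consent terms. Without this, the new 7.1 would contradict the deletion rule.

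The cost is one extra form per visit, with no added examination or imaging, plus an amendment to the data rules. Rare events will stay imprecise, and late harms can be compared only by sequence.

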# Information on statistics, data analysis

Data analysis will be carried out at the Institute for Clinical Epidemology and Applied Biometry of the University of Tübingen.

# Data management

The patient data are registered and stored in a database at the Clinic for Trauma and Restorative Surgery, BG Klinik Tübingen. The deletion of the data which are related to the study is scheduled to take place in 10 years. Only the principal investigator and the authors of this study as well as research associates which have been selected by the authors of the study are authorized to access these data. The data will only be shared only in a pseudonymized fashion, id necessary. In case of a drop out or of the revocation of the permission by the patient, the data will be completely deleted. For the publications resulting from this project, only pseudomynized data will be used.

# Ethical considerations, insurance

## 10.1 Declaration of Helsinki

The Declaration of Helsinki is applicable to this study.

## 10.2 Insurance

No specific personal insurance nor travel accident insurance will be effected. The study protocol will be reviewed by the competent ethics committee.

# General provisions, agreements, organisational procedures

## 11.1 Information on funding

The study is funded by the section´s own budget.

## 11.2 Publications

Publications are composed by the principal investigator of the study (author of the study).

## Annex:

## Appendix 1: Perimed patient information form

## Appendix 2: SF-36 questionnaire

## Appendix 3: Consent form
